### Secondary (clinical) outcome measures

Those who are deemed eligible to participate in the trial will be sent an individualised weblink to complete baseline (T0) clinical outcome measures. These can be completed on paper if the participant prefers. The paper forms will be returned to the research assistant for inputting into the online database and then securely destroyed.

Clinical outcome measures will be completed at baseline (T0) and at 8 weeks (T1), 16 weeks (T2) and 26 weeks (T3). The proposed clinical outcome measures and the domains being measured include:

#### Health-related quality of life/functioning

WHO Disability Assessment Schedule 2.0.^23^EuroQol 5-Dimension-5-Level Health Scale.^24^ICEpop CAPability measure for Adults.^25^

#### Subjective cognitive symptoms

Multifactorial Memory Questionnaire.^26^

#### Depression and anxiety

PHQ-9.^27^GAD-7.^28^

#### ACT-specific measure of change

Acceptance and Action Questionnaire II (AAQ-II)^29^ is a measure of psychological flexibility/inflexibility widely used in ACT. This would potentially be the primary outcome measure in a future definitive RCT.

#### Service utilisation and other cost variables

The Adult Service Use Schedule (AD-SUS)^30^ is a self-report service use questionnaire completed by the study participant in an interview with a trained researcher. The AD-SUS was developed by the study economist for previous work in similar populations and has been adapted for the needs of this study so that participants can complete this without assistance.

#### Improvement

Clinical Global Impression-Improvement Scale,^31^ single item, participant rated.

#### Measure of satisfaction

Satisfaction rating of treatment (single-item, 5-point Likert scale).

The various research activities and outcome measures and the time points when they are collected are listed in table 1.

**Table 1 T1:** Protocol schedule of procedures for the ACT4FCD study

	Screening	Baseline (T0)	2 months (T1)	4 months (T2)	6 months (T3)
Enrolment					
Consent to contact obtained by clinical staff in DMC, CNC or NPC	x				
Informed consent	x				
Contacted by RA to arrange screening interview	x				
Screening					
Diagnostic criteria for FCD	x				
Risk Assessment	x				
Demographics	x				
Comorbidities	x				
Medications	x				
PHQ-9	x				
GAD-7	x				
Randomisation allocation		x			
Interventions		ACT+TAU	Intervention completed		
Assessments					
AAQ-II		x	x	x	X
MMQ		x	x	x	X
WHODAS 2.0		x	x	x	X
EQ-5F-5L		x	x	x	X
PHQ-9		x	x	x	X
GAD-7		x	x	x	X
AD-SUS		x			X
ICECAP-A		x	x	x	X
CGI-I					X
Likert 5-point satisfaction scale				x	
AEs/SAEs		x	x	x	X
Qualitative interviews					
Informed consent for qualitative interview (select participants)		x	x		
Qualitative interviews with select sample of participants		x	x		

AAQ-II, Acceptance and Action Questionnaire II; ACT4FCD, Acceptance and Commitment Therapy for Functional Cognitive Disorder; AD-SUS, Adult Service Use Schedule; AEs, adverse events; CNC, cognitive neurology clinic; DMC, diagnostic memory clinic; EQ-5F-5L, EuroQol 5-Dimension-5-Level; GAD-7, Generalised Anxiety Disorder 7; GCI-I, Clinical Global Impression-Improvement; ICECAP-A, ICEpop CAPability measure for Adults; MMQ, Multifactorial Memory Questionnaire; NPC, neuropsychiatry clinic; PHQ-9, 9-question Patient Health Questionnaire; RA, Research Assistant; SAE, serious adverse event; TAU, treatment as usual; WHODAS 2.0, WHO Disability Assessment Schedule.

### Participant payment

Participants will receive a non-contingent payment of £25 for taking part in the trial. To aid retention, participants will receive £10 at each time point clinical outcome measures are fully completed. Those who take part in the optional qualitative interviews (see below) will also receive an additional £20 incentive.

### The ACT intervention

The group consists of psychoeducation about normal memory functioning, including the roles of attention and normal patterns of forgetting. The psychoeducation element aims to reduce the threat of cognitive symptoms. In line with the ACT model, the aim is to increase psychological flexibility (our proposed primary clinical outcome measure for a future RCT; AAQ-II) in response to the symptoms and associated thoughts and feelings.

The concept of ‘secondary suffering’ is introduced.^32^ It is suggested that attempts to control cognitive ‘failures’ leads to additional suffering, such as ruminations, negative predictions and avoidance. It is explicitly stated that the intervention does not aim to reduce ‘primary suffering’ (the cognitive symptoms), although it is possible that improvements may occur if secondary suffering is reduced. Brief mindfulness practices are incorporated in the group to facilitate ‘bottom-up’ processing, acceptance and more neutral interpretations of unwanted experiences. Value-based goals are identified throughout the sessions in order to shift away from avoidance-based behaviour and the focus on cognitive symptoms.

Participants will be given the time of all ACT sessions prior to randomisation and are asked to consent only if able to attend should they be randomised to the active intervention. They will sent an email with link and diary invite for all the sessions the week before the first session and follow-up reminder calls/emails each week to maximise attendance and engagement despite their memory problems. If a participant fails to attend a session, they will receive a follow-up call from the research assistant to ensure they had the time and link and to enquire about future attendance.

The intervention protocol (see online supplemental appendix 4) will be amended in response to specific feedback received during the contemporaneous qualitative interviews which are designed to explore the participants experience of and satisfaction with the groups.

10.1136/bmjopen-2023-072366.supp4Supplementary data

The intervention group will also receive TAU, as below.

### Treatment as usual

TAU was selected as the fairest comparison, given that is what most patients in the UK currently receive within mental health and cognitive neurology settings. It consists of an explanation of the FCD diagnosis, provision of additional information about the diagnosis and underlying factors (such as medications, chronic pain or poor sleep hygiene; information: https://www.neurosymptoms.org/en/symptoms/fnd-symptoms/functional-cognitive-symptoms), and signposting to local psychological services in primary care (IAPT) for appropriate treatment, such as CBT, when comorbid anxiety and/or depression have been identified. TAU will be delivered as part of routine clinical care by the recruiting service.

### Withdrawal and non-adherence

Participants who do not attend the ACT intervention sessions or complete outcome assessments are not replaced. Disclosed reasons for withdrawal, non-adherence or loss to follow-up are reported.

### Sample size

This is a feasibility trial; as such, a power calculation is neither possible nor necessary. Rather, the sample size is pragmatic. Target recruitment is 48 patients in total (24 in each treatment arm), which provides sufficiently reliable estimates of feasibility outcomes such as recruitment, adherence and retention rates to inform a fully powered RCT. For example, assuming 70% of those approached consent to participate in the trial, the 95% CI for adherence rate would have width of 13.0%. For those in the treatment arm, the 95% CI for an intervention adherence rate of 80% would have width of 16.0%. A sample size of 48 is also consistent with those recommended for pilot and feasibility studies to provide adequate data and precision of means and variances (n between 24 and 50).^33–35^ If it proves challenging to recruit participants via these routes alone then we will approach colleagues at other specialist services in London who see patients with FCD to increase our recruitment pool.

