**Methods and analysis:**

We aim to recruit 48 participants randomised 50:50 to either the ACT intervention and treatment as usual (TAU), or TAU alone. ACT will be provided to participants in the treatment arm following completion of baseline outcome measures. Completion of these outcome measures will be repeated at 8, 16 and 26 weeks. The measures will assess several domains including psychological flexibility, subjective cognitive symptoms, mood and anxiety, health-related quality of life and functioning, healthcare utilisation, and satisfaction with care and participant-rated improvement. Fifteen participants will be selected for in-depth qualitative interviews about their experiences of living with FCD and of the ACT intervention.

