### Primary outcome measures and progression criteria

The feasibility study is primarily gathering data on the feasibility of conducting a future definitive RCT. The primary outcome measures (and progression criteria) are:

Rate of successful recruitment (≥70% intended participants recruited).Rate of successful adherence (≥75% in ACT+TAU attend four or more sessions).Acceptability of the ACT intervention (qualitative interview themes and majority (≥75%) satisfied/very satisfied on 5-point Likert scale).Signal of efficacy (based on increased psychological flexibility following intervention).

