### Statistical analysis plan

A fully documented statistical analysis plan (SAP), centred on describing key process measures to decide if a definitive trial is feasible, will be prepared by the statistician (SAP), formally agreed with coinvestigators and the trial steering committee (TSC) prior to data collection being completed. Participant throughput will be summarised in an extended Consolidated Standards of Reporting Trials (CONSORT) diagram.^36^ The CONSORT flow chart will be used to present descriptive data on trial referral, enrolment, intervention allocation, adherence and retention and to document any deviations from protocol.

Feasibility outcomes will be summarised using descriptive statistics, with 95% CIs provided to permit assumptions when planning a future definitive trial. Data relating to referral, screening and enrolment, and recruitment logs will be used to produce accurate estimates of eligibility, consent and recruitment rates.

Treatment assignation, intervention adherence (eg, ACT session attendance) and satisfaction of care data will be used to contribute to the evaluation of the acceptability of randomisation and allocated intervention/treatment arms. At each time point, the time taken (per participant) to complete trial measures will be recorded. Retention rates will also be estimated for each of the patient-reported/clinical outcome measures, with consideration given to differential dropout between the arms of the trial to identify potential (attrition) bias in treatment completion and/or data collection. All feasibility outcomes will be compared with full-trial progression criteria.

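### The 13.0% and 16.0% confidence-interval widths given in support of n=48 are half-widths, and the first is attached to a rate that matches neither its assumption nor its apparent denominator

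*Protocol article*

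**What the plan says.** The Sample size section sets the target: "Target recruitment is 48 patients in total (24 in each treatment arm"). It calls this size pragmatic and says that it "provides sufficiently reliable estimates of feasibility outcomes such as recruitment, adherence and retention rates". Two worked examples follow.

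- First example: "assuming 70% of those approached consent to participate in the trial", it says, "the 95% CI for adherence rate would have width of 13.0" per cent. No denominator is given.
- Second example, for the treatment arm: "the 95% CI for an intervention adherence rate of 80% would have width of 16.0" per cent.

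The section then adds a separate ground, that 48 lies within a recommended range of 24 to 50 for pilot and feasibility studies.

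Two other places bear on these figures. Primary outcome measures and progression criteria defines adherence in the ACT arm only and sets a threshold: "Rate of successful adherence (≥75% in ACT+TAU attend four or more sessions"). The Statistical analysis plan section says that feasibility outcomes will be reported "with 95% CIs provided to permit assumptions when planning a future definitive trial".

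**The concern.** The width of a confidence interval is its upper limit minus its lower limit. Nothing in the article redefines the word as a margin of error. If the two figures are really half-widths, a reader who takes the text literally will think the intervals are half as wide as they are on the same inputs.

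The first example raises a second question. It starts from a proportion of people approached who consent and ends with an interval for adherence. These are different rates with different denominators.

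These examples are the only figures in the article that quantify the precision of the feasibility rates. Adherence is also a progression criterion, so its precision affects how firmly the trial can place it against 75%.

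**Working it through.** **Inputs from the documents.** Total n=48, with 24 per arm (Sample size; the 1:1 allocation is confirmed in the abstract). Confidence level 95%, so z=1.96. Rates of 70% (first example) and 80% (second example). Stated widths of 13.0 and 16.0 points.

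**Formula.** Wald interval for one proportion: half-width h = 1.96 × √(p(1−p)/n); full width = 2h.

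**Step 1. Reproduce the stated figures.**

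- First example, p=0.70, n=48: h = 1.96 × √(0.21/48) = 1.96 × 0.06614 = 0.1296, or 12.96 points. Full width 25.9 points (57.0% to 83.0%).
- Second example, p=0.80, n=24: h = 1.96 × √(0.16/24) = 1.96 × 0.08165 = 0.1600, or 16.00 points. Full width 32.0 points (64.0% to 96.0%).

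Both printed figures match the half-width to the stated decimal.

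**Step 2. Could another method give them as full widths?**

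| Example | Wald | Wilson | Agresti-Coull | Clopper-Pearson |
|---|---|---|---|---|
| 70%, n=48 | 25.9 | 25.1 | 25.3 | 27.3 |
| 80%, n=24 | 32.0 | 30.9 | 31.8 | 34.6 |

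No method comes near 13.0 or 16.0.

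**Step 3. What n would make the literal widths true?** Solving 2h = w gives n = 4 × 1.96² × p(1−p)/w².

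- 70%, w=0.13: 4 × 3.8416 × 0.21/0.0169 = about 191.
- 80%, w=0.16: 4 × 3.8416 × 0.16/0.0256 = about 96.

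The first cannot be rescued by taking 191 as the number approached: 70% of 191 is about 134 consenting, not 48.

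**Step 4. Which rate does the first example describe?**

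- As a consent rate, the denominator is those approached. The article does not give that number. Assuming that 48 are the 70% who consent, it is 48/0.70, about 69. Then h = 1.96 × √(0.21/69) = 10.8 points, full width 21.6 points.
- As adherence in the ACT arm, n=24. At 70%, h = 1.96 × √(0.21/24) = 18.3 points, full width 36.7 points.

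Neither yields 13.0. Of the denominators tried (24, 48 and 69), only 48 does, and all 48 recruited participants have consented by definition.

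**Step 5. Sensitivity to the assumed 69.** The Recruiting sites and participants section places the eligibility screening interview after consent. More than 48 may therefore have to consent, and more than 69 be approached. With 100 approached (illustrative), h = 1.96 × √(0.21/100) = 9.0 points, full width 18.0 points. Over 69 to 100 approached, the full width runs from 21.6 down to 18.0 points, still above 13.0.

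**Step 6. Effect on the adherence example.** Read literally, a width of 16.0 around 80% is 72% to 88%. The interval on the stated inputs is 64% to 96%. The lower limit moves from 3 points below the 75% threshold to 11 points below it.

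**The case against.** The strongest reply is that little depends on these figures. The size is declared pragmatic, the examples are illustrative, and the 24 to 50 recommendation is an independent ground. No analysis or threshold uses 13.0 or 16.0, and the actual intervals will be reported at the end. All of this stands. It limits the harm but does not make the statement correct.

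A second reply is that *width* is loosely used for margin of error. That is very likely how the slip arose, but the text gives the reader no sign of it.

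A third is that the first example may have meant a rate among all 48, such as retention, for which ±13.0 at 70% would be right. That is possible, but the sentence ties the 70% to consent among those approached, so it would still need rewriting.

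Some stronger readings are tempting and should not be drawn:

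- *The two figures are the only support for n=48.* They are not; the section also gives the pragmatic rationale and the recommended range.
- *Precision is overstated exactly twofold throughout.* The factor of 2 is exact on n=48 and n=24. Re-based to 69 approached, the first example is off by 21.6/13.0, about 1.7.
- *The protocol states a wrong denominator.* It states none; 48 is inferred because it reproduces the figure.
- *The literal interval would have cleared the 75% threshold.* It would not, since 72% is already below 75%. The error understates how far below the interval reaches.
- *The progression rule or the interval method must therefore change.* How often the 75% rule passes or fails is the same whatever the width is called, and the choice of interval method is properly left to the statistical analysis plan.

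**Conclusion.** The statement is wrong as written. Both figures are Wald half-widths presented as widths; the full widths on the matching inputs are 25.9 and 32.0 points. The second example leaves no room for doubt, because its rate, arm and arm size are all stated: 80% adherence among 24 gives about 64% to 96%.

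The first example has a further fault that is visible in the text, a consent assumption joined to an adherence label. That its 13.0 rests on n=48 is an inference from reproduction, though no coherent alternative was found. The replacement width of about 21.6 points rests on the assumption of 69 approached.

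The error concerns the stated precision only. It does not show that 48 is too few for a feasibility trial.

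**What to change.** Amend the two examples in the Sample size section.

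- Second example: *With 24 in the ACT arm, an adherence rate of 80% would have a 95% CI of ±16 points (width 32 points).*
- First example: replace adherence rate with consent rate and base it on the number approached, stating that number as an assumption. For instance: *Assuming about 69 approached (48/0.70) and 70% consenting, the 95% CI for the consent rate would be ±10.8 points (width about 21.6 points).* If a rate among all 48 was meant, name that rate, detach the 70% from consent, and give ±13.0 points (width 25.9 points).

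The cost is wording only. Sample size, conduct and progression criteria are unchanged. The downside is that the published precision looks less favourable, and the claim of sufficiently reliable estimates will be read against intervals of that size.

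### The stated precision for adherence rests on a normal-approximation (Wald) half-width, which at 24 participants and 80% falls short of 95% coverage; the planning interval should be restated as Wilson or Clopper-Pearson limits (minor)

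*Protocol article*

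**What the plan says.** The Sample size section of the protocol article calls the size pragmatic and then defends it on precision. "Target recruitment is 48 patients in total (24 in each treatment arm"), it says, and it judges this enough for reliable estimates of recruitment, adherence and retention. Two worked examples follow. The first reads "assuming 70% of those approached consent to participate in the trial, the 95% CI for adherence rate would have width of 13.0" per cent. The second, for the ACT arm, reads "For those in the treatment arm, the 95% CI for an intervention adherence rate of 80% would have width of 16.0" per cent. Neither names an interval method.

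On the analysis, the Statistical analysis plan section says: "Feasibility outcomes will be summarised using descriptive statistics, with 95% CIs provided to permit assumptions when planning a future definitive trial". Again no method is named, and the detail is deferred to a separate SAP.

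The adherence criterion, under Primary outcome measures and progression criteria, is "Rate of successful adherence (≥75% in ACT+TAU attend four or more sessions"). It is written as an observed rate.

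**The concern.** The two examples are the only numbers offered to show that 24 per arm is precise enough. Both look like the textbook normal approximation for a proportion. With a small sample and a rate well above one half, that approximation is known to be poor. The interval is symmetric about the observed rate when it should reach further down than up, and it becomes too short as the observed rate nears 100%.

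Adherence is a primary outcome, and the article says that its confidence intervals are meant to inform the definitive trial. If lower limits are too high, the planners of that trial would take the adherence rate to be more secure than 24 participants can show.

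**Working it through.** **Inputs.** n = 24 in the ACT arm and 48 in total, planning rates of 80% and 70%, and the 95% level (taken as two-sided, z = 1.96) all come from the Sample size section. The 75% threshold comes from the progression criteria. The first example states no denominator; n = 48 is inferred because it reproduces the figure.

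**Step 1: reproduce the stated figures.** Wald half-width = z × √(p(1 − p)/n).

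- 80%, n = 24: 1.96 × √(0.8 × 0.2/24) = 1.96 × 0.0816 = 0.1600, or 16.0 points.
- 70%, n = 48: 1.96 × √(0.7 × 0.3/48) = 1.96 × 0.0661 = 0.1296, or 13.0 points.

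Both match, but as half-widths. The full Wald widths are 32.0 and 25.9 points.

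**Step 2: rule out other methods.** Half of the full width, in points:

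| Method | 80%, n = 24 | 70%, n = 48 |
|---|---|---|
| Stated | 16.0 | 13.0 |
| Wald | 16.0 | 13.0 |
| Wilson | 15.4 | 12.6 |
| Agresti-Coull | 15.9 | 12.6 |
| Clopper-Pearson | 17.3 | 13.7 |

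Of the four methods, only Wald matches both figures.

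**Step 3: exact coverage at n = 24 and a true rate of 80%.** For each count x from 0 to 24, form the Wald interval, check whether it contains 80%, and add up the Binomial(24, 0.80) probabilities.

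- The interval lies wholly above 80% at x = 22, 23 and 24, where the lower limits are 80.6%, 87.8% and 100%. Probability: 0.0815 + 0.0283 + 0.0047 = 0.1145.
- The interval lies wholly below 80% at x ≤ 14, where the upper limit is at most 78.1%. Probability: 0.0126.
- Coverage is 1 − 0.1145 − 0.0126 = 0.8729. The optimistic share of the misses is 0.1145/0.1271 = 90%. The nominal error is 2.5% on each side.

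The Wald upper limit passes 100% from x = 21 upwards, and at 24/24 the interval has zero width.

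**Step 4: other true rates, n = 24.**

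| True rate | Wald coverage | Wilson coverage |
|---|---|---|
| 75% | 93.9% | 97.0% |
| 78% | 91.5% | 95.6% |
| 80% | 87.3% | 95.9% |
| 82% | 92.7% | 97.2% |
| 85% | 88.8% | 96.0% |
| 90% | 91.3% | 97.2% |

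Clopper-Pearson covers 98.3% at 80%. For n = 48 at 70%, Wald covers 92.8%, Wilson 94.3% and Clopper-Pearson 97.4%.

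**Step 5: the planning intervals under better methods.** Wilson limits are [p + z²/2n ± z√(p(1 − p)/n + z²/4n²)] / (1 + z²/n). At 80% and n = 24, z²/n = 0.160. The centre is (0.8 + 0.080)/1.160 = 0.7586 and the half-width is 0.1542.

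| Method | 80%, n = 24 | Full width | 70%, n = 48 | Full width |
|---|---|---|---|---|
| Wald | 64.0–96.0% | 32.0 | 57.0–83.0% | 25.9 |
| Wilson | 60.4–91.3% | 30.9 | 56.0–81.1% | 25.1 |
| Clopper-Pearson | 58.8–93.4% | 34.6 | 55.1–82.4% | 27.3 |

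80% of 24 is 19.2, which is not a possible count. At the nearest count, 19/24, the limits are 62.9–95.4% (Wald), 59.5–90.8% (Wilson) and 57.9–92.9% (Clopper-Pearson), so the rounding does not alter the picture.

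**The case against.** The strongest reply is that a normal-approximation formula in a planning illustration does not bind the analysis. A reader might infer from the 16.0 and 13.0 that the trial will report Wald intervals. The article does not say so: its analysis section promises 95% intervals and names no method, and the SAP, which is not at hand, may name another. This part of the objection stands. Leaving the method to the SAP is no fault, and the point has to rest on the figures that the article does state.

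A reader might also infer that the progression decision is at risk. It is not. The adherence criterion is met or missed on the observed rate. At 22/24 the Wald lower limit (80.6%) is above 75% while Wilson (74.2%) and Clopper-Pearson (73.0%) are below it. But 22 is the only count from 18 to 24 at which Wald and Wilson disagree about 75%, it occurs about 8% of the time if the true rate is 80%, and 22/24 = 91.7% passes the criterion whichever interval is reported.

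It is also fair to say that 87% lies near a low point of a coverage curve that oscillates with the true rate. That tempers the headline figure but does not remove it: 80% is the article's own planning value, and all six rates checked fall short of 95%.

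Finally, the choice of method hardly alters planned precision. The Wald full width lies between Wilson's and Clopper-Pearson's, and all three lower limits at 80% are well under 75%. In size, the larger defect in the same sentence is that a half-width is called a width. That is also correct, and giving full limits cures both.

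**Conclusion.** The point holds in a limited form and is minor. An interval presented as 95%, and used to argue that the sample is precise enough, rests on an approximation that covers about 87% at the article's own planning rate and about 87–94% across the rates checked from 75% to 90%. At 80%, roughly nine in ten of its misses overstate adherence. In practice, the planning interval sits too high, with a lower limit of 64% where better methods give 59–60%. Lower limits computed in the same way from the results would carry that optimism into the definitive trial.

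The sample size and the progression decision are unaffected. The conclusion assumes that both stated figures come from the Wald formula, an inference from two matches and not something the article says; that the second denominator is 48; and that all 24 ACT participants contribute to the adherence rate as independent binomial observations.

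**What to change.** In the Sample size section, replace the stated width for 80% adherence among 24 participants with full limits: about 60% to 91% (Wilson) or 59% to 93% (Clopper-Pearson). Restate the 70% example in the same way, with its denominator; for 48 this is about 56% to 81% (Wilson) or 55% to 82% (Clopper-Pearson). Add a sentence, matched in the SAP, that the feasibility proportions will be reported with Wilson or Clopper-Pearson 95% intervals. If the SAP already specifies a method, bring the planning figures into line with it.

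The cost is a few words and a slightly less favourable lower limit. Clopper-Pearson also gives a somewhat wider interval (34.6 points against 32.0). No additional participants or data are needed.
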